#### 2.13.2. Safety Analysis

Adverse events: The rates for the CEMR and UEMR groups, the point estimate of the intergroup differences, and the 95% CI will be calculated based on the safety analysis set. Fisher’s exact test will be used for intergroup comparisons.

#### 2.13.3. Exploratory Analysis

An analysis considering the untraceable cases (missing values) will be conducted. If follow-up EGD cannot be performed, the events of the 1-year RFS cannot be observed, potentially affecting the primary endpoint. Therefore, sensitivity analysis considering missing values will be conducted for the primary endpoint. Missing cases in both groups will be randomly imputed to match the proportion of the presence or absence of recurrence or all-cause mortality in the population, excluding cases in which follow-up EGD was not performed from the FAS. The 1-year RFS will be aggregated for each group, intergroup differences will be calculated, and the 95% CI for both groups will be determined using the bootstrap method. Additionally, the 1-year RFS will be calculated for the FAS population, excluding cases where follow-up EGD is not performed, with SNADET recurrence or any deaths considered. Intergroup comparisons will be conducted using the same method described above to confirm that the results remain unchanged.

Moreover, post hoc analysis using multivariate analysis may be conducted to adjust for confounding factors, detect interactions, and explore prognostic factors and predictive markers.

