### 2.10. Sample Size Calculation

The sample size is calculated based on the primary endpoint, 1-year RFS, to assess the non-inferiority of UEMR to CEMR.

Based on previous studies, the histological complete resection rate of CEMR for SNADET is reported to be 92–100% [2,14,24]. However, these reports are all retrospective studies with relatively short follow-up durations, which could result in a lower 1-year RFS. In this trial, the 1-year RFS in the standard treatment (CEMR) group is set at 97%. Additionally, the non-inferiority margin is set at 5%. This margin was defined as the maximum acceptable absolute excess risk of recurrence at 1 year. Prior studies of endoscopic resection for SNADETs reported very low recurrence rates under standard management. In this low-event-rate setting, an absolute margin is considered clinically interpretable. The prespecified margin of 5% was determined through multidisciplinary clinical consensus, balancing a small allowable increase in recurrence risk against the anticipated procedural advantages of UEMR.

Although the significance level of the trial is typically one-sided at 0.025 [25], the probability of decision-making error in the population with tumors at 0.05 (1 out of 20) is not considered unreasonably high according to clinical trial principles. Considering that a one-sided significance level of 0.05 was accepted in previous studies on rare diseases [12], a one-sided significance level of 0.05 is set for this study. This significance level was selected to maintain statistical feasibility in a rare disease setting with an expected extremely low event rate.

Based on these considerations, assuming a 1-year RFS of 97% for CEMR and expecting UEMR to perform equivalently, with a one-sided α error of 0.05, a non-inferiority margin of 5%, and ensuring 80% statistical power, the required sample size was calculated to be 288 cases for conducting a non-inferiority test. Considering ineligible cases and an approximately 10% dropout rate, the target enrollment number was set at 320 cases.

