#### 2.13.1. Analysis of Efficacy

The analysis of efficacy will be based on the FAS as the primary analysis population. A similar analysis will be conducted separately for the PPS. Subgroup analysis will also be performed according to preoperative biopsy status (present vs. absent), tumor length (<10 mm vs. ≥10 mm), and lesion location (bulb vs. other portions), which are allocation adjustment factors. Furthermore, an analysis of cases of untraceability (missing values) will be conducted, considering the inability to perform follow-up EGD.

Analysis of primary endpoint

The 1-year RFS, the primary endpoint, will be aggregated for each group, and the intergroup difference and the 95% confidence intervals (CI) will be calculated. The null and alternative hypotheses for the non-inferiority test are as follows:

Null hypothesis: 1-year RFS of UEMR, P1 + Δ ≤ 1-year RFS of CEMR, P2 (UEMR is inferior to CEMR by more than Δ)

Alternative hypothesis: 1-year RFS of UEMR, P1 + Δ > 1-year RFS of CEMR, P2 (UEMR is not inferior to CEMR by more than Δ)

If the null hypothesis is rejected at a one-sided 5% significance level in the non-inferiority test, we will conclude that UEMR is not inferior to CEMR. If non-inferiority in the 1-year RFS is demonstrated in the primary analysis, a test for superiority will be conducted.

2.Analysis of Secondary Endpoints
a.*En bloc* resection rate, histological complete resection rate, technical success rate, complete mucosal closure rate, and complete mucosal closure rate with standard clips: The rates for the CEMR and UEMR groups, the point estimate of the intergroup differences, and the 95% CI will be calculated.b.Total procedural, resection, and mucosal closure times: Summary statistics will be computed for both groups. The Wilcoxon rank-sum test will be used.c.One-year duodenum preservation survival rate: The rates for the CEMR and UEMR groups, the point estimate of the intergroup difference, and the 95% CI will be calculated.d.Device cost: Summary statistics will be computed for each group, and the Wilcoxon rank-sum test will be used for comparison.

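### The imputation check for patients without follow-up EGD is worded to give a bootstrap interval per arm, not for the difference, and would be noisy near the margin if the random fill-in is done once

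*Protocol article*

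**What the plan says.** Section 2.9.1 treats a patient whose follow-up EGD could not be done as free of recurrence. Section 2.13.1 promises that "an analysis of cases of untraceability (missing values) will be conducted", and section 2.13.3 describes two such checks on the primary endpoint.

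1. **Imputation.** "Missing cases in both groups will be randomly imputed to match the proportion of the presence or absence of recurrence or all-cause mortality" seen in the full analysis set (FAS) patients who had the EGD. RFS is then summarised per group, differences between groups are calculated, and "the 95% CI for both groups will be determined using the bootstrap method".
2. **Complete case.** Patients without the EGD are left out. The groups are compared by the method just described, to confirm that the result does not change.

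For the primary analysis, section 2.13.1 pairs the between-group difference with a 95% CI and states its hypotheses in terms of that difference and the margin. Section 2.10 sets the design: "assuming a 1-year RFS of 97% for CEMR and expecting UEMR to perform equivalently", "a one-sided significance level of 0.05 is set for this study", and "the non-inferiority margin is set at 5" percentage points.

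**The concern.** There are two linked weaknesses.

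**The interval.** Non-inferiority is a statement about the difference between the arms. Two separate intervals, one per arm, cannot be set against a margin of 5 points. Followed literally, the imputation check gives a point estimate of the difference and nothing to judge it by. The complete-case check inherits the problem.

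**The fill-in.** The steps are listed as impute, aggregate, bootstrap, with no mention of repeating or combining draws. At an event rate near 3%, few events are imputed. A single draw would then often add none, which leaves the primary dataset unchanged, or would add one or two in an arm by chance. In a trial close to the margin, that chance can decide whether the check supports the primary conclusion, and that is where the check is most needed.

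**Working it through.** **The plan's own figure.** Inputs from section 2.10: RFS 97% in both arms, margin 0.05, one-sided alpha 0.05, power 80%.

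n per arm = (1.645 + 0.842)² × 2 × 0.97 × 0.03 / 0.05² = 143.9, so 144, or 288 in total. Then 288 / 0.90 = 320. Both stated numbers reproduce ("ensuring 80% statistical power, the required sample size was calculated to be 288 cases").

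**Why per-arm intervals do not answer the question.** Take 8 UEMR and 5 CEMR events among 160 per arm, with Wald limits:

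- UEMR: 152/160 = 95.0%, SE 1.72 points, 95% CI 91.6 to 98.4%.
- CEMR: 155/160 = 96.9%, SE 1.38 points, 95% CI 94.2 to 99.6%.
- Difference: -1.9 points, SE = √(1.72² + 1.38²) = 2.20 points, 95% CI -6.2 to +2.4.

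Only the last line can be compared with -5.

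**Noise of a single draw.** The number of patients without the EGD is an assumption. I use 8 to 16 per arm of 160 (5% to 10%); the upper end borrows the dropout allowance in section 2.10. Each missing patient is drawn independently at the observed event proportion, either by arm or pooled. To measure a verdict at all, I supply an interval for the difference: the one-sided 5% Wald lower limit, compared with -5 points.

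*No event imputed, at a 3% rate:*

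- 16 missing in total: 0.97^16 = 61%.
- 32 missing in total: 0.97^32 = 38%.

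The filled dataset then equals the primary one. If matching the proportion instead means a fixed count, 16 × 0.03 = 0.48 per arm rounds to 0, with the same result.

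*One borderline dataset: 6 UEMR and 4 CEMR observed events, 16 missing per arm.*

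| Events after fill-in (UEMR v CEMR) | Lower limit (points) | Verdict |
|---|---|---|
| 6 v 4 (none added) | -4.45 | pass |
| 7 v 4 | -5.22 | fail |
| 7 v 5 | -4.74 | pass |
| 8 v 5 | -5.50 | fail |

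One extra imputed UEMR event turns a pass into a fail. Summed over all possible draws, 64% pass with imputation by arm and 71% with pooled imputation.

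*Chance that two independent draws disagree.* For a dataset with pass probability p this is 2p(1-p), averaged exactly over the binomial distribution of observed events with CEMR RFS at 97%:

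| Missing per arm | UEMR RFS 97% | UEMR RFS 96% |
|---|---|---|
| 8 | 5-6% | 8% |
| 16 | 8-9% | 12% |

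The ranges cover imputation by arm and pooled.

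**Does repetition help?** Take 7 v 5 observed events with 16 missing per arm. A single draw by arm passes with probability 0.49. Multiple imputation with 1,000 draws and Rubin's rules gave lower limits between -5.25 and -5.33 points in 20 repeats, so the verdict was the same every time. With 6 v 4 it gave -4.92 to -5.02, so a result lying on the margin can still tip.

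**The case against.** The document never says that the imputation is done once. Its wording is compatible with imputing inside each bootstrap resample, and the number of draws and the seed are details that a condensed article may leave to the full protocol or analysis plan. That stands: a reader might infer a single draw, but the text does not establish it, so every seed figure above is conditional on that reading.

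A reader might also infer that no interval for the difference will be produced. That is too strong. The same sentence says that differences are calculated, the next check is called an intergroup comparison by the same method, and the primary analysis pairs the difference with a CI. The phrase about both groups may be loose wording. What stands is that, read literally, it attaches the interval to the arms, unlike the wording in section 2.13.1.

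It is also tempting to say that the verdict depends on the seed in general. It does so only near the margin. With 16 missing per arm, 99% of draws pass at 4 v 4 observed events, and under 2% pass at 8 v 4. With 4 missing per arm, two draws disagree in only about 3% of trials at 97/97. The 10% allowance in section 2.10 also covers ineligible cases, whom section 2.13 removes from the FAS, so 16 per arm is towards the high end.

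Frequent agreement with the primary dataset comes mostly from the low imputed event rate, not from drawing once. Nor would robustness go untested: the complete-case check needs no random draw, and at 7 v 5 events with 16 missing per arm its lower limit is -5.3 points against -4.7 for the primary rule. Finally, these checks sit under an exploratory heading with no decision rule of their own.

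**Conclusion.** The point holds in limited form. As worded, the imputation check attaches its bootstrap interval to each arm and not to the difference on which non-inferiority is judged, and the complete-case check takes over that wording. This part rests on the text alone.

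The second part is conditional on a single draw, on 8 to 16 patients per arm lacking the EGD, and on a Wald limit standing in for the bootstrap. Under those assumptions, the fill-in adds no event with probability 61% to 38% at a 3% rate. Two draws contradict each other in about 5-9% of trials at 97/97 and 8-12% with UEMR at 96%. A borderline 6 v 4 dataset with 16 missing per arm passes in 64-71% of draws.

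The documents do not support saying that the primary conclusion is at risk. It rests on the test in section 2.13.1, which this leaves untouched. The matter is still worth settling before outcome data are seen, because these are the two checks planned for the rule that counts unobserved patients as successes.

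**What to change.** Amend section 2.13.3, or the matching text in the analysis plan, to say that:

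- the imputation is repeated within every bootstrap resample (at least 1,000), or is a multiple imputation with a similar number of draws;
- the event proportion used is either by arm or pooled, chosen in advance;
- both missing-data checks report one interval for the UEMR minus CEMR difference, at the level of the primary decision, with its lower limit compared with -5 points;
- per-arm intervals, if given, are descriptive only.

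The cost is a few lines of analysis code and a sentence or two of text. No new data are needed and the primary test does not change. A result lying exactly on the margin may still vary slightly between runs.

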#### 2.13.4. Patient and Public Involvement

Neither patients nor the public were involved in planning the study design or leading the clinical trial.

### 2.14. Ethics and Dissemination

The D-CURE trial is being conducted in compliance with the Declaration of Helsinki. This trial was approved by the certified review board of Tohoku University (No.34158; 22 November 2023). Necessary modifications will be made to the protocol after the research group reaches a consensus and will be approved by the certified review board of Tohoku University before implementation. If there are any protocol modifications, they will need to be approved by the certified review board of Tohoku University. The principal investigator or physician in charge of the research will obtain free and voluntary written consent for participation in the research after fully explaining the research to the patients using explanatory documents (Supplemental Material File). Written informed consent will be obtained from all patients who wish to participate in this study. The patients will be informed that they can withdraw their consent at any time. Patient data will be anonymized before entry into the database to protect privacy. The project principal investigators will have access to their own clean dataset. The trial findings will be disseminated in peer-reviewed journals and conference presentations.

## 3. Discussion

ER is widely used for the treatment of epithelial tumors of the digestive tract, and various ER methods have been reported [26,27,28]. Numerous clinical trials have demonstrated their efficacy and safety [29,30]. Although CEMR is commonly performed to ensure an adequate margin from the muscularis propria before resection, it requires a certain level of endoscopic skill and incurs additional time and costs. Furthermore, drawbacks, such as hematoma formation owing to submucosal injection and challenges in resection caused by the non-lifting of lesions, have been encountered. To address these shortcomings, UEMR, which eliminates the need for submucosal injections, has been developed [11]. Several reports indicate that UEMR can help achieve a higher *en bloc* resection rate and lower recurrence rate, and is more effective than CEMR, especially for colorectal polyps larger than 10 mm [31,32,33]. However, considering the short-term outcomes in previous reports on SNADETs, demonstrating the superiority of CEMR over UEMR in the duodenum remains challenging [15]. Given that local recurrence is the most important outcome in clinical practice, we planned an RCT to establish the non-inferiority of UEMR to CEMR in terms of the local recurrence rate. UEMR not only offers a simpler technique but also does not require specialized devices. Based on the results of the D-CURE trial, widespread adoption of UEMR for the ER of SNADETs is anticipated, along with the dissemination of UEMR techniques.

A recent prospective observational study was conducted in Japan to evaluate the treatment of SNADETs ≤ 20 mm [12]. This study included 155 patients who underwent UEMR from multiple centers. The *en bloc* and histological complete resection rates were 89.8% and 66.9%, respectively, with a 1-year non-recurrence rate of 97.2%. However, our D-CURE trial has several strengths compared to previous studies. First, this is the first RCT conducted across 40 institutions in Japan, enabling the demonstration of safety and efficacy through random allocation and comparison, thus mitigating the possibility of selection bias observed in single-arm prospective trials. We aim to establish the efficacy, safety, and cost-effectiveness of UEMR based on robust results from the D-CURE trial. Additionally, the D-CURE trial includes mucosal closure as a component of the treatment protocol following resection. Mucosal closure has been shown to significantly reduce postoperative complications such as delayed bleeding and perforation by protecting the submucosal and muscular layers from bile and pancreatic juice. Although mucosal closure is considered essential, it is effective only when the ulcer bed is completely covered by the mucosa [34,35]. Although various closure methods using suturing devices have been reported, a simple and cost-effective method is preferred. Because the ulcer bed after UEMR tends to be smaller than that after CEMR, owing to the absence of submucosal injection, suturing with standard clips may be easier. Therefore, in this study, we specified a protocol to use standard clips as the primary method for closure. This approach may highlight differences in the complete mucosal closure rate achieved with standard clips between CEMR and UEMR.

In interpreting the results of this trial, the prespecified non-inferiority margin of 5% should be understood within the specific clinical context of endoscopic treatment for superficial non-ampullary duodenal epithelial tumors. Reported recurrence rates after standard endoscopic resection are low, and when recurrence occurs, it is typically local and amenable to repeat ER. Therefore, a limited increase in recurrence risk does not necessarily translate into irreversible harm or deterioration in long-term prognosis. From this perspective, the selected margin represents a clinically acceptable trade-off when balanced against the potential advantages of UEMR, including procedural simplicity. In addition, although a one-sided significance level of 0.05 was adopted to ensure statistical feasibility in this rare disease setting with an expected low event rate, the findings should be interpreted with appropriate caution. To enhance the robustness of the conclusions, sensitivity analyses using more stringent non-inferiority margins will be conducted, and effect estimates with confidence intervals will be emphasized rather than reliance on a single *p*-value threshold.

One of the limitations of our study is that it is an open-label study. Blinding endoscopists is not feasible during an endoscopic intervention. However, the primary endpoint, 1-year RFS, is not influenced by the endoscopist’s judgment. The inclusion of death from any cause in the primary endpoint may be considered a stringent outcome measure for a study primarily focused on local recurrence after endoscopic intervention. However, given the minimally invasive nature of the procedure and the expected low mortality in this study population, the primary endpoint is anticipated to largely reflect recurrence events rather than mortality. In addition to UEMR, there are methods that use GEL instead of water and partial injection EMR [36], which involves localized injections. However, owing to additional costs and the effort required to perform localized injections, these techniques have not become as widely adopted as UEMR. Furthermore, applying ESD or more advanced-full thickness resection to lesions under 20 mm that can be completely resected with a snare is not considered optimal owing to high complication rates and technical difficulty [15]. Therefore, UEMR was selected for the study arm.

The D-CURE trial will provide crucial information for decision-making regarding the treatment of SNADETs ≤ 20 mm. We anticipate that the most suitable ER method for patients with gradually increasing SNADETs will be firmly established based on solid evidence from the D-CURE trial.

### Trial Status

The study protocol was approved by the certified review board of Tohoku University (no. 34158; 22 November 2023). The trial was registered in the University Hospital Medical Information Network (UMIN) Clinical Trials Registry (UMIN000052778; 17 November 2023). The first patient was randomized on 18 December 2023. The study is expected to end by 30 November 2027.

## Data Availability

No new data were created or analyzed in this study. Data sharing is not applicable to this article.

## Abbreviations

Underwater endoscopic mucosal resection (UEMR), sporadic non-ampullary duodenal epithelial tumors (SNADETs), conventional endoscopic mucosal resection (CEMR), randomized controlled trial (RCT), endoscopic resection (ER), endoscopic submucosal dissection (ESD), Standard Protocol Items: Recommendations for Interventional Trials (SPIRIT), University Hospital Medical Information Network (UMIN), over-the-scope clip (OTSC), esophagogastroduodenoscopy (EGD), recurrence-free survival rate (RFS), Electronic Data Capture (EDC), UMIN Internet Data and Information Center for Medical Research (UMIN INDICE), full analysis set (FAS), per-protocol set (PPS), confidence intervals (CI).
